**Fig. 2 Fig2:**
[figure not shown]
Flow of study design

### Participants

A total of 171 students aged 13 to 16 years old and attending co-educational secondary schools voluntary participated in the present study. All secondary schools in Singapore were invited to participate in the study via e-mail through publicly available contact details. The research team also attended a meeting with school principals to invite their schools to participate in the study. The three secondary schools whose principal granted permission were included in the study, and approval for data collection at the schools was also obtained from Singapore Ministry of Education. After the department head and PE teachers selected two classes at their school, a researcher attended their PE lessons and explained the risks and benefits of the study to the students by distributing information sheets and informed consent forms. They also had the opportunity to ask questions about the study requirements prior to completing and signing an informed consent form. Students were asked to pass the information sheets and informed consent forms to their parents and discuss their participation in the study with them. Students who gave their consent and returned the informed consent forms signed by their parent were eligible to participate in the study. Parents who consented were asked to complete a brief demographics and socioeconomic status questionnaire. Students who did not return the signed informed consent forms or could not participate in PE lessons were excluded from the study. They participated in PE lessons together with their classmates, but did not do any tasks for the study.

The pilot study by Chatzisarantis et al. [21] reported that their TPB-based intervention with mixed (between and within-subjects) design had a small effect on adolescents’ PA participation (ƞ_p_^2^ = .01) and large effects on their beliefs (ƞ_p_^2^ = .15). Therefore, a conservative small effect size of ƞ_p_^2^ = .02 (*f* = .14) was adopted to calculate the total sample size with G*Power version 3.1.9.2 [22]. It was estimated that a sample of 174 participants was required to achieve a power of .90 at the alpha level of .05 for the repeated within-subjects analysis of 6 groups (2 classes at three schools) and 6 measurement points (3 measurement points in two conditions).

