The second factor is related to the types of beliefs communicated during intervention periods. According to the TPB, interventions may target behavioral beliefs by emphasizing salient benefits or de-emphasize disadvantages associated with PA through attitudes (individuals’ positive vs. negative evaluations toward PA) and intentions (the extent to which individuals are willing to exert effort towards performing PA). Alternatively, interventions may target normative beliefs which emphasize the attitudes of significant others (e.g., attitudes of teachers or parents) towards PA. The interventions that target normative beliefs are likely to influence PA participation through subjective norms (individuals’ beliefs about whether significant others approve or disapprove PA participation) and intentions. Further, interventions may assist people to overcome salient barriers by targeting control beliefs. Interventions that target control beliefs are likely to affect PA participation through perceptions of their behavior control (individuals’ beliefs about whether they possess the necessary resources or skills to perform PA or overcome barriers) and intentions. The model underpinning the TPB is presented in Fig. 1. A pilot study was recently conducted to examine the effectiveness of a school-based program in promoting leisure-time PA for secondary school students [21]. The intervention program targeted on salient benefits and barriers to doing PA. To examine the duration of the intervention program, it was conducted over 8 weeks to half of the participants but only for 4 weeks to the other half of the participants. Results of the pilot study revealed that regardless of the intervention duration, the average leisure-time PA increased from the baseline to the midpoint of the intervention period (4 weeks after the baseline) and it was maintained until the end of the program (8 weeks after the baseline). Although these results were encouraging, the pilot study had several limitations. First, the usefulness and cost-effectiveness of the intervention program on reducing BMI were not evaluated. Second, the PA participation was measured only with self-reported questionnaires and the sustained leisure-time PA level was not assessed with an objective measure. Finally, there was no comparison on the effectiveness of the intervention with those who did not receive an intervention as the pilot study did not include a control group.

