### Intervention and fidelity check

PE lessons were conducted twice a week over 4 weeks in both control and intervention conditions. In the control condition, PE teachers encouraged students to participate in PA during leisure time without delivering persuasive messages in PE lessons. An intervention program was implemented after the control period was over (see Fig. 2).

Prior to the intervention period, PE teachers were trained on how to deliver persuasive messages through a 3-h workshop. During the workshop, PE teachers were encouraged to express their concerns about delivering persuasive messages, researchers addressed those concerns to assist PE teachers to conduct the intervention at a sufficient level of proficiency. The persuasive messages targeted salient information related to the benefits and barriers associated with PA, which were identified based on the results of surveys conducted for students at Pre-Baseline in the control condition. Some examples of salient benefits were “health benefits”, “improving physical skills and fitness”, “fun and socialization” and “recommended physical activity level”, whereas salient barriers were “lack of time”, “lack of facilities or equipment”, “feeling tired” and “weather”.

In the intervention condition, PE teachers delivered the persuasive messages that targeted the salient benefits and barriers associated with PA at the last 5 to 10 min of each PE lesson. After PE teachers delivered the persuasive message, students were asked to answer a question about the message in each lesson (e.g., “Please explain briefly how do you know that MVPA improves your fitness levels?”). Researchers evaluated PE teachers’ fidelity of the interventions with a checklist (e.g., “The PE teacher provided clear instructions on this session’s message”) on a scale ranging from 1 (*not at all*) to 5 (*very much*).

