### Data analysis

To examine the first research hypothesis (*H*_*1*_), a 2 (type of conditions: control vs. intervention) × 3 (measurement points: Baseline, Post 1 and Post 2) repeated ANOVA will be conducted on students’ MVPA levels. The second hypothesis (*H*_*2*_) will be examined through a 2 (type of conditions: control vs. intervention) × 3 (measurement points: Pre-Baseline, Post 1 and Post 2) repeated ANOVA on students’ BMI levels. A path analysis will be conducted to examine the third hypothesis (*H*_*3*_) with *M*plus (Version 8) [27]. Student’s age, gender, socio-economic status, and prioritization of PA together with fidelity of intervention programs will be included as covariates in the analyses. Furthermore, correlation analyses will be conducted to examine the relationships between the subjective and objective measures of PA.

A cost effectiveness analysis of the program will also be conducted by focusing on the incremental cost-effectiveness of the intervention condition compared to the control condition. Incremental cost-effectiveness ratios will be calculated in terms of the incremental cost per unit BMI reduction. Differences in BMI between different measurement points (Pre-Baseline, Post 1 and Post 2) will also be calculated. Height will be added as a covariate in the analyses in order to account for the growth change in height over the data collection period. Incremental cost-effectiveness ratios will be calculated using standard techniques coupled with bootstrapping methodology and acceptability curves [28]. Through these analyses, it will provide information about the probability that an intervention is cost-effective.

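### The planning effect rests on a pilot without a control group, and the stated .90 power belongs to a six-occasion omnibus test, not to the comparison of intervention with control

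*Protocol article*

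**What the plan says.** **Source of the effect size.** In the protocol article, the Participants section says that the authors of the pilot "reported that their TPB-based intervention with mixed (between and within-subjects) design had a small effect on adolescents’ PA participation"; the partial eta squared was .01 for activity, against .15 for beliefs. From this it infers that "a conservative small effect size of ƞ_p_^2^ = .02 (*f* = .14) was adopted to calculate the total sample size". The result is that "a sample of 174 participants was required to achieve a power of .90 at the alpha level of .05", and this is attached to one analysis: "repeated within-subjects analysis of 6 groups (2 classes at three schools) and 6 measurement points (3 measurement points in two conditions".

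**What the pilot compared.** The Theoretical framework section says that half of the pilot participants had the programme for 8 weeks and half for 4, that activity rose over time whichever duration was given, and that activity was self-reported only. The missing control group is listed as a limitation: "there was no comparison on the effectiveness of the intervention with those who did not receive an intervention as the pilot study did not include" one.

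**What this trial compares.** All students go through a control condition and then the intervention condition. The control is not inert: "In the control condition, PE teachers encouraged students to participate in PA during leisure time without delivering persuasive messages in PE lessons". The Data analysis section plans "a 2 (type of conditions: control vs. intervention) × 3 (measurement points: Baseline, Post 1 and Post 2) repeated ANOVA will be conducted on students’ MVPA", which is the outcome of H1. Under Implications of study findings, success means more activity relative to the control condition.

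**The concern.** A pilot in which everyone received the programme can yield a change over time, or a difference between the longer and the shorter version. It cannot yield the difference between programme and no programme. The article names this as a weakness of the pilot, yet bases its planning effect on the same pilot without adjustment or caveat. It gives no other basis for .02 as the size of the increment over an encouragement control.

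The test behind the .90 is also not the test of that increment. A comparison of all six occasions responds to any difference among them, including a rise within the control phase. The claim that the messages add something to encouragement rests on the condition × time term.

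At stake is how a null H1 will be read. If .90 is taken as the chance of showing that the messages beat the control condition, a non-significant result looks like good evidence that they add nothing. The article gives no support for that degree of assurance.

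**Working it through.** **Inputs.** From Participants: partial eta squared .02 adopted, .01 for the pilot's effect on activity, alpha .05, k = 6 groups, m = 6 measurement points, N = 174 required, N = 171 enrolled. From Data analysis: a 2 × 3 repeated ANOVA, so condition × time has (2 − 1)(3 − 1) = 2 df.

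**Formula.** Noncentral F for a within-subjects term with d numerator df:

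- f² = η²/(1 − η²)
- df2 = (N − k)·d
- λ = f²·df2
- power = P(F′(d, df2, λ) > the .95 quantile of F(d, df2))

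Sphericity is assumed, and no clustering is allowed for beyond the six groups.

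**Step 1: reproduce the plan.** With η² = .02, f² = .02/.98 = .0204 and d = 6 − 1 = 5. The smallest N with power of at least .90 is 169, which rounds up to 174 for six equal groups. This is the stated figure.

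- N = 174: df2 = 168 × 5 = 840, λ = 17.14, power .911.
- N = 171: df2 = 165 × 5 = 825, λ = 16.84, power .905.

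The article does not say which effect-size option of the software was used. The default option with a correlation of .5 gives 72, so the option used here is inferred because it returns 174.

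**Step 2: the term that compares the conditions over time.** Same formula, d = 2.

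| Partial η² of condition × time | N | df2 | λ | Power |
|---|---|---|---|---|
| .02 | 174 | 336 | 6.86 | .64 |
| .02 | 171 | 330 | 6.73 | .63 |
| .01 | 174 | 336 | 3.39 | .36 |
| .01 | 171 | 330 | 3.33 | .35 |

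Power .90 on this term would need 318 students at .02 and 636 at .01 (rounded up to a multiple of six). These figures show scale only and are not a target.

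**Step 3: sensitivity to the control response (assumed).** Suppose .02 described an uncontrolled change on this term, and encouragement alone produced a share c of that change. The increment is then f·(1 − c), so f² is multiplied by (1 − c)². The documents give no value for c.

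| c (assumed) | f² | Partial η² | Power, condition × time, N = 174 |
|---|---|---|---|
| 0 | .0204 | .020 | .64 |
| 25% | .0204 × .5625 = .0115 | .011 | .40 |
| 50% | .0204 × .25 = .0051 | .005 | .20 |

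The scaling is applied to the 2-df term only. In the 5-df omnibus test a rise in the control phase adds to the differences among the six means and does not subtract out.

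**The case against.** **The arithmetic is right and the paragraph names its test.** Both are true. The .90 is correct for the analysis entered, and the article never says in words that it is the power for intervention against control. The fault lies in letting it stand as the only power figure for a trial whose H1 is that comparison.

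**The .02 is a nominal small effect, not the pilot's value.** This is largely right: the pilot's effect on activity was .01. It does not rescue the figure. The article derives .02 from the pilot results and calls it conservative, but it is twice the value for the outcome in H1, and nothing else supports it for the controlled contrast.

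**The bias may not run in a known direction.** This stands. A reader might infer that the pilot effect must overstate the increment, because part of an uncontrolled rise would also occur under the control condition. That holds only if the pilot figure is a change over time. The article says only that the pilot's design was mixed, so the figure could equally be a contrast of durations. For the same reason no fixed reduction of f² can be derived from the documents.

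**The students have already taken part, and planning from the nearest pilot is common.** This is fair, and the article discloses the missing control group. It limits the remedy to wording and a power table.

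**Conclusion.** The point holds in a limited form. The pilot effect does not estimate the intervention-minus-control effect, the adopted .02 is not justified for that contrast, and .90 should not be read as the power to show that the messages beat the control condition. At the 171 enrolled, the omnibus test has power .905 at .02, whereas condition × time has about .63 at .02 and about .35 at .01. These values rest on sphericity and on the inferred effect-size option.

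A reader might go further and conclude that the trial's true power for H1 is now known to be low. The documents do not support that: they give no incremental effect and no control response, so the .40 and .20 are illustrations under assumed shares. Nor do they show that 174 was miscalculated; it reproduces.

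**What to change.** In the sample size paragraph (Participants):

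1. State that the pilot had no control group and that its effect does not estimate the intervention-versus-control effect.
2. Say that .90 applies only to the omnibus test across six occasions at an assumed partial eta squared of .02, and no longer call .02 conservative when the pilot's effect on activity was .01.
3. Restate power at 171 students for the condition × time term: about .63 at .02 and about .35 at .01, with sphericity stated as an assumption.
4. Add a short sensitivity table on that term for the unknown control response, labelled as assumed, for example .64, .40 and .20 at shares of 0%, 25% and 50% for N = 174.

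The cost is a reworded paragraph and one small table. No students or data are added. The drawback is a less favourable stated power.

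### The planning effect of partial eta squared .02 is called conservative, but it is twice the pilot's effect on physical activity, the outcome of H1

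*Protocol article*

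**What the plan says.** The sample-size paragraph (protocol article, Methods/design, Participants) starts from a pilot with a mixed between- and within-subjects design. The pilot's intervention "had a small effect on adolescents’ PA participation", given as partial eta squared .01, and a large effect on beliefs, given as .15. The next sentence draws the planning value from these two figures: "Therefore, a conservative small effect size of" partial eta squared .02 (f = .14), on which the total sample size is based. The result follows: "It was estimated that a sample of 174 participants was required to achieve a power of .90 at the alpha level of .05", for a repeated within-subjects analysis with 6 groups and 6 measurement points. The section reports 171 participating students.

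H1 (Aims of the study) concerns participation in moderate-to-vigorous PA during leisure time. Under Data analysis it is tested by a 2 × 3 repeated ANOVA on MVPA levels. Beliefs enter through H3, as mediators.

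**The concern.** A planning effect is conservative when it lies at or below what the evidence suggests. Of the two pilot figures, the one in the domain of H1 is .01, and the planning value is twice that. The sentence opens with a word of inference, so .02 is presented as following from the pilot. No other ground is offered, such as a smallest effect worth detecting.

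The paragraph gives the article's only stated power. A reader faced with a null H1 result will set it against .90 and may take it as evidence that the programme does not work. If the true effect were the size the pilot found for PA, that reading would be unsafe.

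**Working it through.** **Inputs from the Participants section.** Alpha .05; target power .90; k = 6 groups; m = 6 measurements; planning partial eta squared .02 (f = .14); pilot PA value .01; N = 174 required, 171 enrolled.

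**Not stated, so assumed.** Nonsphericity epsilon = 1. The G*Power effect-size option and the correlation among repeated measures are not given, so I looked for settings that return 174.

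**Effect sizes.** f² = η²/(1 − η²).
- At .02: f² = .02/.98 = .02041, f = .1429 (stated as .14).
- At .01: f² = .01/.99 = .01010, f = .1005.
- Ratio of f: .1429/.1005 = 1.42.

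**Step 1: reproduce 174.** Power comes from the noncentral F distribution, with df2 = 5(N − 6) and N in multiples of 6. Three settings return 174:
- A. Within-factor test, *as in SPSS* option: df1 = 5, λ = f²(N − 6)·5. With f² = .02/.98, λ = .02041 × 168 × 5 = 17.14 and power is .911. At the next lower N, 168, power is .899.
- B. Within-factor test, *as in Cohen* option: df1 = 5, λ = f²·N·5. With f = .14, λ = .0196 × 174 × 5 = 17.05 and power is .909. At 168 it is .898.
- C. Default option, group-by-time interaction with correlation .3: df1 = 25, λ = f²·N·6/(1 − .3). With f = .14, λ = .0196 × 174 × 6/.7 = 29.23 and power is .903. At 168 it is .889.

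The default option's within-factor test did not return 174 at correlations 0, .3, .5 or .7; it gave 144, 102, 72 and 48.

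**Step 2: change only the effect, to .01.**

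| Setting | λ at 174 | Power at 174 | Power at 171 | N for .90 |
|---|---|---|---|---|
| A | .01010 × 168 × 5 = 8.48 | .590 | .581 | 336 |
| B | .01010 × 174 × 5 = 8.79 | .608 | .599 | 330 |
| C | .01010 × 174 × 6/.7 = 15.06 | .548 | .538 | 336 |

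Across the three settings, power at .01 is .55 to .61 with 174 students and .54 to .60 with 171. The N for .90 is 1.9 times the stated one (330/174 = 1.90; 336/174 = 1.93).

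**The case against.** The best defence has four parts.

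- **The calculation is not in error, and nothing is hidden.** The stated inputs give 174, and .01, .15 and .02 appear in adjoining sentences. This stands. The fault lies in how the input is justified and labelled.
- **.02 is conservative against .15, and H3 concerns beliefs.** True, but the label is not limited to beliefs, and H1 is about activity. Planning on a target above a pilot estimate is legitimate if it is called a target.
- **The pilot's .01 may not be the relevant effect.** The article's Theoretical framework section says the pilot compared 8 with 4 weeks of the programme and had no control group. The article does not say whether .01 belongs to time, duration or their interaction, and partial eta squared depends on the design and its error term. This stands, and it makes the loss of power conditional. It does not rescue the label, because the article itself uses this figure as its basis.
- **The G*Power settings are inferred.** This stands too. Under the default option's interaction test, power at .01 with 174 students would be .74 at correlation .5 and .96 at .7. Those settings do not return 174, however, so they do not appear to be what was used.

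Two stronger readings are tempting. A reader might infer that .01 is itself too high, since the pilot was uncontrolled and relied on self-report. The article gives no direction for such a bias, and if .01 came from comparing two active durations it could understate the effect against control. A reader might also quote the power of a 2-df condition-by-time test at .01, about .35 to .36 with 171 students. That figure mixes in a different issue: the calculation used other degrees of freedom than the 2-df test, whose power is already only .63 to .65 at .02.

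**Conclusion.** The point holds as a misdescribed planning assumption. For the H1 outcome, .02 is twice the cited pilot estimate (1.42 times in f), so it is optimistic by the article's own evidence.

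Its size is a drop from .90 to roughly .54 to .61 if the pilot's .01 is the true effect, assuming epsilon = 1 and one of the three settings that reproduce 174. A reader might infer that the trial has been shown to be underpowered for H1, or that 174 is wrong. Neither follows: 174 is correct at .02, and the true effect in this within-subjects design is unknown. The shortfall of 171 against 174 is immaterial here.

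This should be fixed. It does not rank higher because enrolment is complete and no hypothesis or test depends on the adjective.

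**What to change.** In the sample-size paragraph:
1. Delete *conservative* and the inference that .02 follows from the pilot.
2. State that .02 is a target effect, twice the pilot's partial eta squared for PA participation, and give the reason for choosing it.
3. Beside the .90, report that power at .01 is roughly .54 to .61 for 171 to 174 students. Name the G*Power option, correlation and epsilon actually used. If they differ from those assumed here, recompute the figure.

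Do not enrol more students on this account, and deal with the power of the 2-df interaction separately. The cost is two or three sentences and a less favourable stated power; no data, test or hypothesis changes.

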### Procedure

Prior to the commencement of the study in each condition, students’ body compositions (e.g., height, body mass and body fat percentage) were measured at their school. Height was measured using a ruler attached to the wall to the nearest 0.5 cm, body mass and body fat percentage were measured with a body composition monitor (Omron Karada Scan: HBF-362). Students were also asked to complete a demographics sheet and a set of self-report measures of leisure-time PA and psychological variables (Pre-Baseline). After completing the questionnaire set, students were instructed to wear the GENEActiv (Original) accelerometer (Activinsights Ltd, Cambridgeshire, UK) on their non-dominant wrist for one week to objectively measure frequency and intensity of their PA level (Baseline). When students returned the accelerometer, they were also asked to complete another set of the same self-report measures (Baseline). Subsequently, students spent four weeks in the control or intervention condition. During the 4 weeks, an intervention program was conducted in PE lessons in the intervention condition. After the 4 weeks, students were requested to wear the accelerometer again for one week across two occasions (Post 1 and Post 2) with a 4 weeks interval period in between before measuring their body compositions and completing the same set of self-report measures. Students’ height, body mass and body fat percentage were measured at three occasions (Pre-Baseline, Post 1 and Post 2) in each condition (see Fig. 2).

